## Abstract

**Introduction::**

Premenstrual dysphoric disorder (PMDD) is a serious form of premenstrual syndrome with mental symptoms as its main manifestation, which seriously affects women's health and daily life. Some basic research and clinical studies have shown that the Chinese herbal medicine of Xiaoyaosan can relieve the symptoms of mental disorders with few side effects. The aim of this study is to evaluate the clinical efficacy of Xiaoyaosan for treating PMDD with liver-qi depression syndrome. In addition, metabonomics and small molecular marker compounds closely related to the pathogenesis of PMDD are expected to be found, and mechanism of Xiaoyaosan is further explored from the metabolic level.

**Methods and analysis::**

This study is a clinical pilot trial. Thirty PMDD patients with liver-qi depression syndrome and thirty healthy participants will be recruited. Study participants will be assigned in a 1:1 ratio to 2 groups: a normal control group and Xiaoyaosan treatment group. The treatment group will receive the Chinese patent medicine of Xiaoyaosan for 3 menstrual cycles. The primary outcome is the syndrome change in the Daily Record of Severity of Problems (DRSP). The secondary outcome is improvement in TCM syndrome, which will be measured with TCM symptom score scale. Urine metabolism profiles of participants by liquid chromatograph-mass spectrometer (LC-MS) method will be measured to explore the mechanism of PMDD pathogenesis and action of Xiaoyaosan on PMDD.

**Discussion::**

This trial will evaluate the effectiveness and the therapeutic mechanism from the metabolomics level of Xiaoyaosan in individuals with PMDD. If successful, the outcome of this trial will provide a viable treatment option for PMDD patients and objective evidence on the efficacy of Xiaoyaosan for PMDD.

**Ethics and dissemination::**

The trial has been approved by the Institutional Ethics Committee of Dongzhimen Hospital Affiliated to Beijing University of Chinese Medicine (file number: DZMEC-KY-2019-73). Written informed consent will be obtained from all participants. The results of the study will be published in peer-reviewed journals or communicated via yearly reports to funding bodies.

**Trial registration::**

Chinese Clinical Trial Registry, ChiCTR1900026296.

## Introduction

1

Premenstrual syndrome (PMS) refers to the periodic physical, mental and behavioral changes of women in the luteal phase.^[1]^ Premenstrual dysphoric disorder (PMDD) is a serious form of PMS.^[2]^ Mental symptoms are the main characteristics of PMDD, such as depression, anxiety, irritability, and so on, appearing in the late luteal phase and ending shortly after menstruation.^[3]^ The incidence of PMDD varies from 3% to 8% for premenopausal women.^[4]^ Cyclically recurring premenstrual symptoms seriously affect women's health and daily life,^[5]^ are even related to suicidal ideation.^[6]^ The pathogenesis of PMDD is still insufficiently clear, studies indicate that many factors can cause PMDD, such as hormonal changes, neurotransmitters, diet, stress, and so on.^[7,8]^ The comorbidities of PMDD with other mental disorders are high, a retrospective study showed that more than 50% of women with PMDD had diagnosis of major depression disorder.^[9]^ The therapeutic goal of PMDD is to relieve premenstrual emotional and physical symptoms.^[10]^ In most cases, pharmacotherapy of antidepressants is the main therapy, such as selective serotonin reuptake inhibitors (SSRIs) and other serotonergic antidepressants.^[11]^ The antidepressant medications have positive antidepressant-like effects, but a range of side effects cannot be ignored, such as fatigue, nausea, decreased libido, sweating, and so on.^[11]^

Traditional Chinese medicine (TCM) has been widely used in the treatment of mental disorders in China. An epidemiological study of PMDD based on TCM theories shows that the liver dysfunction is the major pathogenic feature in clinical syndrome differentiation and the liver-qi depression syndrome is an important subtype.^[12]^ Xiaoyaosan, a Chinese herbal formula, was first described in *Taiping Huimin Heji Jufang* during the Song Dynasty of China (960–1127 AD). It has the effect of dispersing stagnated liver qi for relieving qi stagnation. The formula has been used to treat mental disorders for thousands of years in China.^[13,14,15]^ Xiaoyaosan consists of Radix Bupleuri (root of Bupleurum Chinense DC.), Radix Paeoniae Alba (root of Paeonia lactiflora Pall.), Radix Angelicae Sinensis (root of Angelica sinensis (Oliv.) Diels), Rhizoma Atractylodis (root and rhizome of Atractylodes lancea (Thunb.) DC.), Poria (fungus nucleus of Poria cocos (Schw.) Wolf), Radix Glycyrrhizae (root and rhizome of Glycyrrhiza uralensis Fisch.), Herba Menthae (aboveground portions of Mentha haplocalyx Briq.), and Rhizoma Zingiberis Recens (fresh root and rhizome of Zingiber officinaleRosc.) in a ratio of 5:5:5:5:5:4:1:1.^[16]^ At present, Xiaoyaosan is still widely used in clinical treatment of mental disorders. Modern study has shown that Xiaoyaosan can exert antidepressant-like and anxiolytic-like effects effectively. Our research group has reported a large number of studies on the underlying mechanism of action of Xiaoyaosan. For example, Xiaoyaosan can promote the reduction in oxidative-stress-induced hippocampus neuron apoptosis.^[17]^ Xiaoyaosan reduces stress-induced depression by regulating the tryptophan metabolism, Apelin-APJ system, the brain-derived neurotrophic factor (BDNF) and its receptors, and the expression of normalized glial fibrillary acidic protein in hippocampus.^[18–21]^ In addition, Xiaoyaosan can exert antidepressant-like effects by reducing glutamate-induced neuronal damage of frontal cortex and improving the functions of astrocytes and the astrocytic excitatory amino acid transporters.^[22]^ Xiaoyaosan can also improve depressive-like behavior with the modulation of gut microbiota.^[23]^ Similarly, Xiaoyaosan can downregulate the TNF-α/JAK2-STAT3 pathway in the hippocampus and regulate the corticotropin-releasing factor 1 receptor (CRF1R) signaling pathway to reduce stress-induced anxiety behaviors.^[13,24]^

## Objectives

2

This study aims to evaluate the clinical effectiveness of Xiaoyaosan for treating PMDD patients with liver-qi depression syndrome. In addition, metabonomics and small molecular marker compounds closely related to the pathogenesis of PMDD are expected to be found, and mechanism of Xiaoyaosan is further explored from the metabolic level. To achieve this aim, a non-randomized controlled, prospective, pilot trial has been planned.

## Methods and analysis

3

### Trial design

3.1

This is a non-randomized, controlled, prospective, pilot trial designed to evaluate the effectiveness of Xiaoyaosan in treating PMDD with liver-qi depression syndrome for woman. Thirty PMDD participants with liver-qi depression syndrome and thirty healthy participants will be recruited from Beijing University of Chinese Medicine and Dongzhimen Hospital Affiliated to Beijing University of Chinese Medicine. After obtaining written informed consent from participants, 60 participants will be assigned to Xiaoyaosan treatment group and normal control group, respectively with a ratio of 1:1. The intervention period is 3 menstrual cycles. Figure 1 shows the study flow. The schedule of trial enrolment, interventions and assessments is provided in Table 1. The protocol was designed in accordance with the Consolidated Standards of Reporting Trials guidelines.^[25]^

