### Intervention

4.4

Sixty participants will be assigned to Xiaoyaosan treatment group and normal control group respectively with a ratio of 1:1. Participants in Xiaoyaosan treatment group will be required to take Chinese patent medicine with Xiaoyaosan (Xiaoyao Pills, 8 pills) orally with warm water 3 times a day for 3 menstruation cycles continuously. The medicine will be taken from the luteal phase and stopped during the menstrual period of each menstruation. The Xiaoyaosan will be manufactured as pills and provided by Jiuzhitang Co., Ltd. Participants in normal control group will not be intervened. Any other treatments for PMDD will not be allowed during the study. If the condition deteriorates, participants can withdraw from the study and choose modern drug therapy, such as SSRI antidepressants. Study visits will take place at baseline and at 1, 2, 3 menstrual cycle.

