### Primary outcome

5.1

The primary outcome measure is the 21 symptom items of the Daily Record of Severity of Problems (DRSP).^[27]^ The symptoms of 60 participants will be evaluated at baseline and at 1, 2, 3 menstrual cycle by the DRSP. The average of the late luteal (premenstrual) phase for symptom items will be summed to generate the total score. The primary efficacy variable is the changes in symptom score between baseline and after 3 menstrual cycles of Xiaoyaosan treatment. In addition, the symptom score of Xiaoyaosan treatment group will also be compared with the normal control group.

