## Sample size calculation

8

This study is a pilot study, so a formal sample size calculation is not completely required.^[30]^ A sample size of 60 participants will be recruited, 30 PMDD participants and 30 healthy participants. Results from this study will be applied to the sample size calculations in future studies.

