Current clinical studies on PMDD mainly focus on efficacy evaluation, the potential mechanism of drug action has been ignored. So this trail will study the pathogenesis of the PMDD and the action mechanism of TMC from the perspective of metabonomics along the efficacy evaluation of Xiaoyaosan. The metabonomics and small molecular marker compounds closely related to the pathogenesis of PMDD and efficacy mechanism of Xiaoyaosan by the LC-MS technology are expected to be explored. If the research is successful, the results of this trial could provide preliminary objective evidence on the efficacy of Xiaoyaosan for PMDD and more accurate indication of Xiaoyaosan. Significantly, this trial will provide a novel research method for researchers to improve the effectiveness of TCM. However, the limitations of this study include its small sample size, single-center design and short treatment period. Therefore, the larger-sample, large-scale, multi-center, blind, randomized control and longitudinal clinical trials are still needed.

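### The trial is labelled controlled and promises efficacy evidence, but its only comparison group is untreated healthy women, so neither DRSP comparison can isolate an effect of Xiaoyaosan

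*Protocol article*

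**What the plan says.** Section 3.1 (Trial design) calls the study a "non-randomized, controlled, prospective, pilot trial designed to evaluate the effectiveness of Xiaoyaosan in treating PMDD", and section 2 (Objectives) gives the same label and aim. On allocation, section 3.1 says that "60 participants will be assigned to Xiaoyaosan treatment group and normal control group, respectively with a ratio of 1:1". The abstract has "Study participants will be assigned in a 1:1 ratio to 2 groups", and section 4.4 repeats the idea.

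Section 8 (Sample size calculation) shows who the groups are: "A sample size of 60 participants will be recruited, 30 PMDD participants and 30 healthy participants". Section 4.4 (Intervention) gives Xiaoyaosan to the treatment group and says of the other: "Participants in normal control group will not be intervened". No placebo, active, waiting-list or untreated PMDD group is described.

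Section 5.1 (Primary outcome) makes the change in DRSP symptom score from baseline to after three treated cycles the primary efficacy variable. It adds that "the symptom score of Xiaoyaosan treatment group will also be compared with the normal control group". The secondary outcome in section 5.2 is a percentage reduction in the TCM score from before to after treatment.

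On what success would mean, the abstract's Discussion says that "the outcome of this trial will provide a viable treatment option for PMDD patients and objective evidence on the efficacy of Xiaoyaosan for PMDD". Section 12 (Discussion) is softer: it speaks of preliminary evidence on efficacy and calls for larger blinded randomized trials. Its list reads: "the limitations of this study include its small sample size, single-center design and short treatment period".

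**The concern.** A non-randomized controlled trial of a treatment normally means that patients with the condition received either the treatment or something else, without random allocation. That is not the case here. The 1:1 ratio is a recruitment ratio between two populations, and no woman with PMDD could have entered the other group.

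The label matters because the stated aim is effectiveness and the stated conclusion is efficacy. A reader who accepts the label would take the control group as the guard against placebo response and spontaneous improvement. The healthy group cannot do that job, so the headline claim would rest on an uncontrolled before-after change.

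**Working it through.** **Inputs from the article.** 30 women with PMDD, all treated; 30 healthy women, none treated (sections 3.1, 4.4 and 8); 30 + 30 = 60, which agrees with the stated total. Tests are two-sided at 5% (section 9). No SD, effect size or power is given (section 8), so there is no calculation of the plan's own to reproduce.

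**Step 1: what the before-after change contains.** Four components enter the mean change in the treated group:
- any drug effect;
- placebo response: no placebo or blinding is described, so the women can be presumed to know that they are treated, and section 6 says that participants record the DRSP;
- fluctuation of symptoms between cycles;
- regression to the mean: section 4.1 requires premenstrual daily averages of at least 3.0 on three items and at least 50% worsening from the postmenstrual phase, so entry selects for high premenstrual scores.

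Nothing in the design separates the first component from the other three.

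**Step 2: what the comparison with healthy women contains.** It contrasts treated PMDD with untreated absence of PMDD, so treatment and disease status coincide completely. The healthy women are not selected for high scores and take no pill, so they carry neither the regression to the mean nor the placebo response that would have to be subtracted. At most they could show a drift common to both groups, such as season or assay batch.

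**Step 3: illustration of scale.** Suppose the drug effect is zero and the mean non-drug improvement is d, in SDs of the change score. For a paired t test with n = 30, the critical value is t(0.975, 29) = 2.045, the noncentrality is d × √30, and the chance of P < .05 is the probability that the noncentral t falls outside ±2.045.

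| assumed d | noncentrality | chance of P < .05 |
|---|---|---|
| 0 | 0 | 5% |
| 0.2 | 1.10 | 19% |
| 0.3 | 1.64 | 36% |
| 0.5 | 2.74 | 75% |
| 0.7 | 3.83 | 96% |
| 0.8 | 4.38 | 99% |

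Two caveats apply. The values of d are assumptions. The article names no paired test: for continuous variables section 9 lists only the independent t test and the rank-sum test.

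**Step 4: could non-drug change be of that order?** Under a normal model, the fall from regression to the mean is (1 − r) × λ, where r is the between-cycle correlation and λ is the mean of the selected upper tail in SDs of the score. For selection from the top 20%, λ = 1.40; from the top 5%, λ = 2.06. With r = 0.8 and the top 20%: 0.2 × 1.40 = 0.28 SD. With r = 0.5 and the top 5%: 0.5 × 2.06 = 1.03 SD. Both r and the selection fraction are assumed. These are SDs of the score, not of the change, so they cannot be read straight into the table, but they show that selection alone could produce a shift that is not negligible.

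**The case against.** The best defence is disclosure. The article says that the trial is non-randomized and a pilot, states plainly that the controls are healthy and untreated, and uses the word respectively when describing assignment, so a careful reader would not think that women with PMDD were allocated between arms. Section 12 reduces the claim to preliminary evidence and calls for blinded randomized trials. Section 8 says that the results will feed later sample size calculations. A healthy group is also a sensible reference for the exploratory urine metabolomics in section 5.3.

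Much of this stands, and it limits the point to labelling and strength of claim. It does not remove the point. The word non-randomized implies a treatment comparator that merely lacks randomization. The abstract's claim carries no qualifier. Section 12 still claims efficacy evidence and does not list the missing PMDD comparator.

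Some stronger readings are tempting but unsupported:
- A reader might infer that a non-significant difference from healthy women will be presented as a return to normal. The article never claims normalisation or equivalence; section 5.1 says only that the scores will be compared.
- A reader might infer that any before-after fall with P < .05 will be declared efficacy. No such decision rule is stated.
- A reader might say that there is no control comparison at all, or that all efficacy evidence is self-rated. A concurrent comparison does exist, although it is uninformative about the drug. For the secondary TCM score, section 5.2 has a researcher recording it, while section 6 has participants doing so.

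**Conclusion.** The point holds as a mismatch between the design and what is claimed for it. This is a single-arm before-after study in 30 women with PMDD, alongside a healthy reference group. It can estimate change under treatment; it cannot attribute that change to Xiaoyaosan, and so it cannot deliver the efficacy evidence or the viable treatment option stated in the abstract.

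That conclusion follows from the group definitions alone and needs no numerical assumption. The 36%, 75% and 96% figures are illustrative: they rest on assumed non-drug changes of 0.3, 0.5 and 0.7 SD of the change, a zero drug effect and a paired t test. They show that a before-after test responds to mean change from any cause. They do not measure bias in this trial.

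**What to change.** 1. **Sections 2 and 3.1:** replace the design label with a single-arm before-after pilot in 30 women with PMDD, with a parallel untreated healthy reference group.
2. **Abstract (Methods and analysis), sections 3.1 and 4.4:** replace the 1:1 assignment wording with a statement that diagnosis determines the group and that 30 women are recruited to each.
3. **Section 5.1:** state that the DRSP comparison between the PMDD and healthy groups is descriptive, reported as a difference with a 95% confidence interval, and is not evidence of efficacy.
4. **Abstract (Discussion) and section 12:** limit the conclusion to an estimate of change under treatment, for use in planning a controlled trial.
5. **Section 12, limitations:** add that there is no PMDD comparator and no blinding.

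Keep the healthy group for the metabolomic disease contrast. The changes are wording only: no participants, visits or treatment rules are affected. The cost is a weaker stated claim.

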**Figure 1 F1:**
[figure not shown]
Flow diagram of study design.

**Table 1 T1:**
[figure not shown]
Schedule of enrolment, interventions, and assessments.

### Setting and recruitment

3.2

The study will be conducted in Beijing University of Chinese Medicine and Dongzhimen Hospital Affiliated to Beijing University of Chinese Medicine. Participants will be recruited through Internet advertisement and posters in the university and hospital. In addition, some participants will be recommended via doctors from the gynecology clinic. Those who are willing to participate in this study can contact the researchers by telephone. Participants will be provided detailed information about the study by the researchers.

## Participants

4

### Diagnostic criteria

4.1

The Clinical diagnostic criteria of PMDD is based on the 5th edition of the *Manual of Diagnosis and Statistics of Mental Diseases* (DSM-5).^[2]^ The TCM syndrome of liver-qi depression in the study follows the *Guidelines for Clinical Research of new*

*Chinese Medicine*.^[26]^ In addition, PMS severity criteria should also be met, including the follows:

1.A postmenstrual phase (days 6–10) daily average ≤2.5 for each symptom.2.A premenstrual phase (day −5 to −1 before menstruation) daily average ≥3.0 for 3 distinct items.3.A premenstrual phase daily average worsened by at least 50% compared with the corresponding postmenstrual phase daily average for 3 distinct items.4.A score ≥3 on functional impairment items for at least 1 day during the premenstrual phase.

The diagnostic standards of TCM syndrome of liver-qi depression are as follows:

1.Primary symptoms and signs include premenstrual depression and (or) irritability, breast pain, chest tightness, and ability reduction of work, family management, learning and communicate.2.Secondary symptoms and signs include chest and hypochondriac distention pain, sighing frequently, lower abdomen falling distention, anorexia, fatigue, menstrual abdomen pain, menstrual blood suspending fluid retention, retarded menstruation.3.In addition, the patient has a pale or dark tongue, fat body of tongue, thin white or yellow coated tongue, and a stringy thin or stringy slow pulse.

Patients who meet the following criteria can be diagnosed as PMDD liver-qi depression syndrome: 3 primary and secondary symptoms/signs, combined with the tongue and pulse conditions, symptoms appearing before menstruation and disappearing after menstruation for 2 menstrual cycles or more continuously.

### Inclusion criteria

4.2

Participants of PMDD with liver-qi depression syndrome will be included:

1.Clinical diagnostic criteria of PMDD according to the DSM-5.2.Women aged between 18 and 30 years.3.Regular menstrual cycle of 21 to 35 days (fluctuation range <3d).4.Clear mind and independent judgement.5.Able to sign informed consent and cooperate voluntarily.

Participants of healthy people will be included:

1.Female college students and graduate students, aged between 18 and 30 years.2.Regular menstrual cycle (21–35 days).3.Clear mind and independent judgement.4.Able to sign informed consent and cooperate voluntarily.5.Physical health (Consistent with World Health Organization definition of Health).

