## Discussion

12

PMDD, a severe mental disorder occurring in the luteal phase of women, has a quite negative impact on patient's daily lives. Diagnostically, PMS and PMDD represent the same symptoms,^[31]^ but PMDD is the serious form of PMS.^[32]^ The incidence of PMS is relatively high. About 95% of women of reproductive age have premenstrual symptoms,^[33]^ and 13% to 18% of women need treatment due to PMDD.^[32]^ The common therapy of PMDD is antidepressants. Due to the side effects of drugs for PMDD, such as headache, weight gain, sexual dysfunction, insomnia, and other symptoms, the compliance of patients is rather poor, and then affect the drug efficacy.^[34]^ Therefore, more therapeutic agents than the currently available are needed to improve the quality of these patients life.

Traditional Chinese medicine has a positive effect on improving emotional symptoms and may be the important choice of complementary and alternative medicines for the treatment of PMDD. Chinese herbal medicine treatment is based on the TCM theory of ‘treatment based on syndrome differentiation’. Liver-qi depression provide the crucial pathogenesis of PMDD in the TCM concept. Xiaoyaosan is composed of herbal medicine with the function of regulating emotional factors, which can improve symptoms of depression and anxiety. A Meta-analysis study found that no serious adverse events were reported in ten randomized controlled trials involving Xiaoyaosan intervention.^[35]^ In addition, Compared with antidepressants, Xiaoyaosan plus antidepressants could reduce the adverse reactions.^[35]^ Chinese herbal medicine treatment is based on the TCM theory of ‘treatment based on syndrome differentiation’. Therefore, adding TCM syndrome efficacy evaluation may help to determine more suitable patient populations and optimize indications in this study.

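### Section 4.2 sets no premenstrual-symptom exclusion for healthy controls and different entry rules for the two groups, leaving the PMDD-versus-healthy comparisons open to contamination and confounding

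*Protocol article*

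**What the plan says.** The protocol article lists the entry rules for each group in section 4.2.

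- **Controls:** "Female college students and graduate students, aged between 18 and 30 years"; "Regular menstrual cycle (21–35 days"); clear mind; consent; and "Physical health (Consistent with World Health Organization definition of Health").
- **Patients:** a DSM-5 diagnosis of PMDD; "Women aged between 18 and 30 years"; "Regular menstrual cycle of 21 to 35 days (fluctuation range <3d"); clear mind; consent.

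Section 4.1 gives numerical symptom thresholds for the postmenstrual and premenstrual days, but only as part of diagnosing patients. The exclusion list in section 4.3 is not split by group. It bars recent users of drugs for PMDD, but not women with untreated PMS or PMDD.

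Section 3.2 describes recruitment by advertising in the university and hospital and adds that "some participants will be recommended via doctors from the gynecology clinic", without saying which group these are.

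Section 5.1 records the DRSP in all 60 women at baseline and at cycles 1 to 3. It defines the primary efficacy variable as the change within treated patients and adds a comparison with the control group. Section 5.3 makes urine metabolomics exploratory.

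On frequency, the Introduction states: "The incidence of PMDD varies from 3% to 8% for premenopausal women".

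**The concern.** The control group has two uses: as the reference for the additional DRSP comparison, and as the natural reference for finding urine compounds related to PMDD. Both uses need controls who are free of the disorder and otherwise comparable with the patients.

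The first need is not secured. A general health item with no diary threshold is not an operational screen for a disorder that the Introduction characterises mainly by mental symptoms. Unrecognised cases among controls would shrink the baseline contrast. After treatment they could flatter the drug: they raise the control mean, so treated patients look closer to normal than they are.

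The second need is not secured either. Student status and cycle regularity may go with diet, daily routine and hormonal pattern, any of which could plausibly alter a urine profile. A difference that comes from the entry rules could then be read as a marker of PMDD. Allocation is by disease status, so nothing in the design balances these factors.

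**Working it through.** **1. Entry rules side by side (sections 4.2 and 4.3)**

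| Feature | Patients | Controls |
|---|---|---|
| Age | 18–30 | 18–30 |
| Cycle length | 21–35 days | 21–35 days |
| Cycle fluctuation | below 3 days | no limit |
| Student status | not required | required |
| Premenstrual status | DSM-5 PMDD | no rule; general health item only |
| Exclusion list | common, as written | common, as written |

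Apart from disease status and the health item itself, the rules differ in two respects: student status and cycle fluctuation.

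**2. Expected number of cases among controls**

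There is no figure in the plan to reproduce: the 60 in section 8 is 30 + 30, with no formal calculation.

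Inputs: n = 30 controls (section 8); p = 0.03 to 0.08 (Introduction). Assumption: controls resemble the general population, so the health item removes nobody.

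- Expected cases = 30p: 30 × 0.03 = 0.9; 30 × 0.08 = 2.4.
- Chance of at least one = 1 − (1 − p)^30: 1 − 0.97^30 = 0.599; 1 − 0.92^30 = 0.918.

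**3. Dilution of the contrast**

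Let a share c of controls be cases similar to the patients. The control mean is (1 − c) × healthy mean + c × PMDD mean. The observed baseline difference is then (1 − c) times the true difference. With c = 0.03 to 0.08, the contrast shrinks by 3% to 8%.

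**4. What that dilution does to power**

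The article gives no effect size or standard deviation, so the standardised difference d is assumed. With 30 per group and two-sided 0.05 (section 9), power ≈ Φ(d(1 − c)/√(2/30) − 1.96).

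| Assumed d | c = 0 | c = 0.03 | c = 0.08 |
|---|---|---|---|
| 0.5 | 49.1% | 46.7% | 42.9% |
| 0.73 | 80.7% | 78.3% | 73.9% |
| 1.0 | 97.2% | 96.4% | 94.6% |

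The loss is about 1 to 7 percentage points.

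**5. Confounding**

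This part cannot be sized. The article does not give the share of patients who will be students or the spread of cycle fluctuation among controls.

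**The case against.** Several points on the other side stand.

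- **Health item.** Controls are recruited as healthy, and the Discussion calls PMDD a severe mental disorder, so a woman known to have it is not plainly eligible. The common exclusion list also removes women recently treated for it. The figures above are therefore upper-end. What remains is that the item sets no test for premenstrual symptoms.
- **Where the weakness falls.** The primary efficacy variable is untouched. The comparison with controls is additional, the metabolomics is exploratory, and the study is a declared pilot that names its small sample as a limitation and calls for randomised trials.
- **Condensed article.** How health is verified could be left to a fuller protocol. But the entry rules printed here differ between the groups, which is more than missing detail.

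A reader might also infer more than the text supports.

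- *The comparison is contaminated and confounded.* The rules permit this but do not show that it will happen.
- *Nearly all controls are affected*, because "About 95% of women of reproductive age have premenstrual symptoms". At 95% that is 28.5 of 30, but the figure counts any premenstrual symptom. It does not measure PMDD, and most such women could properly remain as controls.
- *Contamination is 13% to 18%*, from the Discussion's figure for women needing treatment. That sits uneasily with the Introduction's 3% to 8%, which is the article's direct figure for PMDD frequency.
- *Patients are a clinic sample and controls are not.* Section 3.2 does not tie the clinic referrals to patients, and section 3.1 draws the study's participants from the same university and hospital.
- *Age is a confounder by design.* The age band is the same in both groups.

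**Conclusion.** The point holds as a risk built into the entry rules. Section 4.2 does not keep women with PMS or PMDD out of the control group, and it imposes one rule on controls only and another on patients only. The additional DRSP comparison and the urine marker search are exposed; the within-patient primary change is not.

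The dilution is modest: 3% to 8% of the contrast at the article's own frequency, on the assumption that controls resemble the general population and that any hidden cases resemble the patients. The likely figure is lower if the health item works in part. The confounding is of unknown size. It matters most for the urine search, where the healthy group is the only reference for the disease.

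Later adjustment would not fully repair it. With student-only controls, a non-student patient has no counterpart, so adjusting for student status would extrapolate. Removing symptomatic controls after enrolment without a prior rule would mean selecting on the outcome variable. The remedy therefore belongs in the eligibility criteria.

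**What to change.** Change section 4.2 in three places.

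1. Require that healthy participants do not meet the section 4.1 premenstrual severity criteria on their baseline DRSP cycle. The diary must cover postmenstrual days 6–10 as well as the premenstrual days, because the section 4.1 criteria use both and section 5.1 describes only late-luteal scoring.
2. Apply the same cycle-fluctuation rule to both groups.
3. Use the same source population for both groups: drop the student-only restriction, or frequency-match controls to patients on student status.

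**Cost.** The DRSP is already planned at baseline for all 60 women, so no new instrument is needed. Controls must complete the diary cycle, including the postmenstrual days, before they are confirmed, and a few volunteers will be replaced afterwards. Because controls would then be selected partly on the DRSP, the baseline DRSP difference between groups would be partly by construction and should be reported as descriptive.
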